### Study population

Participants will meet the following inclusion criteria: (1) belong to one of the following professions: medical doctors, nurses, orderlies, physiotherapists, psychologists, hospital porters, ambulance drivers, nursing and medical students working in hospitals; (2) aged 18–70 years old; and (3) fluent in the French language. Exclusion criteria include (1) initial score at the Perceived Stress Scale-10 (PSS-10) [30]< 16 (which means that the participant has a non-significant level of stress), (2) suicidal ideation score assessed by the question 9 of the Patient Health Questionnaire - 9 (PHQ-9) [31] > 2, and (3) be under guardianship. Participants will be recruited by psychiatrists or psychologists in six hospitals of the East region of France, i.e., Hôpitaux Universitaires de Strasbourg, Hôpitaux Civils de Colmar, Groupe Hospitalier Régional de Mulhouse Sud-Alsace, Centre Hospitalier Universitaire de Nancy, Centre Hospitalier Universitaire de Besançon, and Centre Hospitalier Universitaire de Dijon; the East region was the region that was the most affected by the COVID-19 in France. Demographic information (gender, age, family situation), medical history, and occupational exposure (i.e., position, service, seniority on the job, working time, COVID-19 infection status) will be collected.

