#### Secondary outcomes

The Patient Health Questionnaire – 2 items version (PHQ-2) [34] will be applied to screen for depression. Each item is scored on a scale ranging from 0 (not at all) to 3 (nearly every day).

The Short Form Posttraumatic Stress Disorder Checklist 5 (SF-PCL-5) [35] will be used to screen for post-traumatic stress symptoms. It consists of 4 items ranging from 0 (not at all) to 4 (extremely).

The Connor-Davidson Resilience Scale – 2 items version (CD-RISC 2) [36] will be used to measure resilience. The 2 items are scored on a scale ranging from 0 (not true at all) to 4 (almost always true).

A short form of the Insomnia Severity Index (ISI) [37] will be used to measure the severity of insomnia using 5 of the initial 7 items of the ISI. Each item is scored on a scale ranging from 0 (not at all) to 5 (extremely).

The Affective Rumination Questionnaire (ARQ) [38] will be applied to measure work-related rumination. The 5 items are rated on a scale ranging from 0 (very rarely or never) to 4 (very often or always).

Self-reported credibility of the treatment will be assessed via the Credibility and Expectancy Questionnaire (CEQ) [39] at baseline and at 8 weeks of treatment. This questionnaire contains 6 items rated either from 1 to 9 or from 0 to 100% and evaluates whether the participants “think” or “feel” that their treatment will be efficient.

Finally, the Client Satisfaction Questionnaire (CSQ-8) [40] will be applied as a self-report measure assessing participants’ satisfaction at the end of the 8-week program. The 8 items are scored on a scale ranging from 1 to 4. Higher scores are indicative of elevated satisfaction.

To measure the perceived efficacy and utility of each individual session of the CBT program, participants will complete visual analog scales (VAS) measuring stress, sleep, self-efficacy, and mood before each session; two VAS will be administered after each session to measure perceived stress and utility of the session.

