### Procedure

Participants will be recruited via (i) the psychological support hotlines established during the COVID-19 outbreak at the 6 hospital sites participating in the study, (ii) the psychologists and psychiatrists who consult with healthcare workers in their departments, (iii) by billposting, and (iv) by posting on the hospital websites and on targeted Facebook groups. An e-mail will be sent to department heads to inform their team members. Subjects interested in taking part in the study will be asked to consult the study website (www.masanteaussi.fr) where they will find a document with information on the aims and the scope of the study. They will then choose a time slot to be called back by an investigator who will assess the subject’s eligibility. Oral information about the study and the randomization procedure will be given to all subjects. Participants will be randomized and assigned to the intervention by the investigator. If the subject is eligible, he/she will receive an e-mail with a username and password allowing him/her to log into the platform after a 24-h period. After receiving the e-mail, participants will be able to make their first connection to the website and sign an electronic informed consent form (previously signed online by the investigator). They will then have to complete the self-report questionnaires assessing symptoms of depression, PTSD, insomnia, resilience, and rumination. Following this, they can either start their first session of the online CBT program or gain access to the bibliotherapy documents.

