Mid-therapy assessment will take place at 4 weeks after inclusion, i.e., subjects will be asked to fill out depression, PTSD, and COVID-19 infection status questionnaires in order to track potential undesirable outcomes. Eight weeks following their inclusion, participants will receive an e-mail inviting them to fill out all the self-report questionnaires. Then, an e-mail will inform them of the end of the program and of the availability of local mental health services if needed, e.g., psychologists, psychiatrists. Three and 6 months after the end of the program, participants will receive an e-mail inviting them to fill out the follow-up self-report questionnaires. At each step (4-week, 8-week, 3-, and 6-month follow-up), undesirable outcomes will be tracked: i.e., when a participant presents with significant suicidal ideation scores on the 9th item of the PHQ-9 (> 1), the investigator is automatically notified by the website and calls the participant to make the appropriate referrals (e.g., psychiatrist); if a participant is hospitalized in a psychiatric facility during the 8-week treatment phase, he or she will be removed from the study. If a questionnaire is not completed 3 days after it is due, the participant will receive a reminder via an e-mail notification. If questionnaires are not completed a week after they are due, one of the investigators will call the participant and invite him/her to complete it. At any time during the intervention period and after completing the program, subjects are free to withdraw their participation without justifying their motives. No further data will be collected for these participants.

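### The protocol uses two unexplained cut-offs on PHQ-9 item 9, so a score of 2 is eligible at entry with no stated action but counts as significant from week 4

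*Protocol article*

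**What the plan says.** The Protocol article uses item 9 of the PHQ-9 in two places.

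- **Entry (Study population).** The second exclusion criterion is "suicidal ideation score assessed by the question 9 of the Patient Health Questionnaire - 9 (PHQ-9) [31] > 2". Scores up to and including 2 are therefore admissible.
- **Follow-up (Procedure).** The alert applies "when a participant presents with significant suicidal ideation scores on the 9th item of the PHQ-9", and the same sentence gives the cut-off and the response: "significant suicidal ideation scores on the 9th item of the PHQ-9 (> 1), the investigator is automatically notified by the website". The investigator then calls the participant and makes a referral. The timing is given just before: "At each step (4-week, 8-week, 3-, and 6-month follow-up), undesirable outcomes will be tracked". Baseline is not among these steps.

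Two other statements bear on the point. Eligibility is judged by telephone: "They will then choose a time slot to be called back by an investigator who will assess" eligibility (Procedure). The depression measure among the outcomes is the two-item form: "The Patient Health Questionnaire – 2 items version (PHQ-2) [34] will be applied to screen for depression" (Secondary outcomes). The full PHQ-9 is mentioned only in the exclusion criterion and in the alert, each time for item 9.

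**The concern.** The protocol labels a score above 1 significant and attaches a definite response to it. Its entry rule, on the same item, lets one of those scores in, and the article neither explains the difference nor says what happens to such a person at entry. Followed as written, a participant who already meets the protocol's own definition on the day of inclusion reaches a score-triggered response only at the 4-week assessment.

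The trial is delivered remotely. It recruits people selected for raised stress (PSS-10 below 16 is an exclusion), partly through psychological support hotlines, and the item-9 alert is the only safety response in the article that is triggered by a questionnaire score. What is at stake is participant safety and uniform handling across six sites, not the efficacy estimate.

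There is also a smaller gap in the listing. The alert relies on item 9, but the outcomes text names only the PHQ-2, and the 4-week battery is described as including a depression questionnaire without naming the instrument. A site that built its batteries from the outcomes text alone would not find item 9 there.

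**Working it through.** The protocol gives no figure to reproduce here. The check sets the two rules side by side over the possible scores.

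**Inputs**

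- Entry rule: exclude if item 9 > 2 (Study population).
- Alert rule: notify, call and refer if item 9 > 1 (Procedure).
- Alert times: 4 weeks, 8 weeks, 3 months, 6 months (Procedure).
- Item range: whole numbers 0 to 3. Secondary outcomes states this range for the PHQ-2. That it also holds for item 9 of the PHQ-9 is an assumption.

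**Applying both rules**

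| Item 9 score | Excluded at entry (> 2)? | Alert at follow-up (> 1)? | Admitted, yet meets the alert definition? |
|---|---|---|---|
| 0 | No | No | No |
| 1 | No | No | No |
| 2 | No | Yes | **Yes** |
| 3 | Yes | Yes | No |

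The scores that count as significant are 2 and 3. The entry rule removes 3 and keeps 2, so exactly one of the two lies between the rules.

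**Following a participant who scores 2 through the Procedure section**

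1. The investigator calls and assesses eligibility. A score of 2 passes. No further step is written for it.
2. Login details arrive by e-mail. After a 24-hour period the participant can connect, give consent and complete the baseline questionnaires online. No alert is stated for this point.
3. The intervention or the brochures become available. The hotline can be called on weekdays from 9 a.m. to 5 p.m., and its psychologists refer callers who present with suicidal ideation. This depends on the participant calling and is not tied to the item score.
4. At 4 weeks the first score-triggered alert applies. An unchanged score of 2 now leads to notification, a call and a referral.

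The score is the same at steps 1 and 4, and the stated response differs.

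**Size.** The article gives no distribution of item-9 scores, so the share of the 120 participants who would enter with a score of 2 cannot be calculated.

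**The case against.** The best defence is that the two rules do different jobs. One decides who may enter; the other decides whom to telephone during remote follow-up. A lower threshold for a call than for exclusion is coherent, and both rules can be carried out exactly as written. A score of 2 at follow-up does not remove anyone; psychiatric hospitalisation during the treatment phase does. This stands: a reader might infer that the rules contradict each other, and strictly they do not. The difference is unexplained, and the entry side has no stated action.

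Nor is the participant unseen at entry. An investigator makes the eligibility call and needs the item-9 score to do so. The article also mentions standardised documents for the inclusion call, which are not shown and may cover the case. This stands too. It narrows the gap to what the article tells the investigator to do.

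The mention of the PHQ-2 might suggest that the alert has no data source. The text does not support that. Procedure itself names the ninth item of the PHQ-9 and the times at which it is used, and a safety item need not appear in a list of outcomes. The body of Table 1 is not shown, and its legend is not a full inventory: it also omits the ARQ, which is a listed outcome. What remains is an inconsistency in naming.

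A reader might also conclude that a comparison of harms between arms could not be interpreted, because follow-up alerts would mix ideation present at entry with new ideation. That goes too far. Statistical analyses plans no comparison of item-9 alerts between arms, and 1:1 randomisation balances ideation at entry in expectation. A raw count of alerts should simply not be read as a count of new events.

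**Conclusion.** The point holds as an unexplained difference between two cut-offs on the same item, with no stated action at entry for a participant who meets the follow-up definition. It concerns one score, 2, on the assumption that item 9 runs from 0 to 3. The gap is in the written response, not in the investigator's knowledge of the score, and it lasts from inclusion to the 4-week assessment.

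This should be corrected because it touches participant safety and costs little. It does not alter the primary analysis, the sample size or any planned comparison between arms. The documents do not show which cut-off is right, and this review takes no position on that.

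**What to change.** 1. Reconcile the exclusion criterion in Study population with the alert in Procedure, or state in one sentence why the two cut-offs differ. The clinical leads choose the rule.
2. State how a person who meets the Procedure definition of significant ideation at entry is to be handled. This choice also belongs to the clinical leads.
3. Name PHQ-9 item 9 as a safety item, separate from the PHQ-2 outcome, at baseline, 4 weeks, 8 weeks, 3 months and 6 months.

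Optionally, when alerts are reported, show them by arm and by whether the participant already met the definition at entry, so that persisting and new ideation can be told apart. This is a descriptive addition and corrects no stated error.

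The cost is a few sentences in the protocol and, if the item is not already programmed at a given time point, one extra question there. Under the protocol's own rule, the modification goes to the ethics committee.

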## Abstract

**Background:**

The acknowledgment of the mental health toll of the COVID-19 epidemic in healthcare workers has increased considerably as the disease evolved into a pandemic status. Indeed, high prevalence rates of depression, sleep disorders, and post-traumatic stress disorder (PTSD) have been reported in Chinese healthcare workers during the epidemic peak. Symptoms of psychological distress are expected to be long-lasting and have a systemic impact on healthcare systems, warranting the need for evidence-based psychological treatments aiming at relieving immediate stress and preventing the onset of psychological disorders in this population. In the current COVID-19 context, internet-based interventions have the potential to circumvent the pitfalls of face-to-face formats and provide the flexibility required to facilitate accessibility to healthcare workers. Online cognitive behavioral therapy (CBT) in particular has proved to be effective in treating and preventing a number of stress-related disorders in populations other than healthcare workers. The aim of our randomized controlled trial study protocol is to evaluate the efficacy of the ‘My Health too’ CBT program—a program we have developed for healthcare workers facing the pandemic—on immediate perceived stress and on the emergence of psychiatric disorders at 3- and 6-month follow-up compared to an active control group (i.e., bibliotherapy).

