## Background

The acknowledgment of the mental health toll of the COVID-19 epidemic both in the general population [1–5] and in healthcare workers [6–11] has increased dramatically in the last few weeks as the disease has grown into a pandemic status.

Indeed, preliminary epidemiological and qualitative findings suggest that the epidemic might have negative immediate as well as long-term mental health effects, particularly in healthcare workers [12]. For instance, in one of the first reports published by a Chinese team, frontline healthcare workers were found to present with extremely high rates of depression (> 50%), generalized anxiety disorder (> 44%), insomnia (> 36%), and stress-related symptoms (> 73%) [13]. Since then, numerous studies have further confirmed these findings in nurses [11, 14], physicians and medical staff [6, 8, 12, 15], and trainees [10, 16] and warranted the need for psychological treatments aiming at relieving immediate stress and preventing the onset of psychological disorders in healthcare workers [12]. To address this need, we developed a 7-session online cognitive behavioral therapy (CBT) program targeting the reduction of stress and the reinforcement of adaptive coping behaviors in healthcare workers during the COVID-19 pandemic. The aim of our randomized controlled trial study protocol is to evaluate the efficacy of the treatment we have designed for healthcare workers—the ‘My Health too’ CBT program—on immediate perceived stress, as well as on the emergence of psychiatric disorders at 3- and 6-month follow-up (Fig. 1).

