### Sample size

The number of subjects required was calculated based on the data from Rose et al. [25] which showed a relative decrease in the PSS-10 score of 15% in the control group and 30% in the experimental group. Mean score values with a standard deviation (< 5) were reported. Given that the healthcare professionals recruited in our study will be under greater stressors than Rose et al.’s [25] study sample, which consisted of college students, the expected values of PSS-10 at baseline are 23 ± 5 with a decrease to 19.6 ± 5 in the control group and 16 ± 5 in the experimental group. Simulations using a mixed linear regression model showed that 46 subjects per group, i.e., 92 in total, would be needed to highlight a difference between groups with a power of more than 90% and an alpha risk set at 5%. Considering an estimation of 10% of exclusions (initial PSS-10 < 16) and 20% of drop-outs, the number of subjects in the study was increased to 120 subjects in total (Fig. 1).

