### Outcomes

#### Primary outcomes

The decrease of the Perceived Stress Scale – 10 items version (PSS-10) [30] score at 8 weeks will be our primary outcome. The 10 items of the PSS range from 0 (never) to 4 (very often); higher scores are indicative of higher perceived stress. The PSS-10 is validated in French [32], and its ease of use and psychometric properties have been widely studied in professional contexts [33]. The expected PSS-10 values are 23 ± 5 initially with a decrease to 19.6 (control group) and 16 (experimental group).

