In order to minimize attrition bias, an intention to treat analysis and specific techniques for handling missing data will be performed. Missing data will be described variable by variable and as a whole in order to search for monotonous patterns. In order to determine the process of generating the missing data (MCAR: missing completely at random, MAR: missing at random or MNAR: missing not at random), dummy variables for whether a variable is missing will be created and cross-tabulated with others observed variables. Multivariate logistic regression can be used to determine a set of variables associated with the probability of observation. In the case of MCAR or MAR processes, multiple imputation methods will be used.

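### Removing participants admitted to psychiatry from the study sits badly with the promised intention-to-treat analysis: on its natural reading it stops outcome collection after a severity-related event, with a bias of unknown direction that is probably small

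*Protocol article*

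**What the plan says.** All references are to the protocol article.

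- **Procedure.** The text on tracking undesirable outcomes ends with the rule that "if a participant is hospitalized in a psychiatric facility during the 8-week treatment phase, he or she will be removed from the study". Removal is from the study, not from the online programme or the brochures.
- **Statistical analyses.** To limit attrition bias, "an intention to treat analysis and specific techniques for handling missing data will be performed". On method, the section says: "In the case of MCAR or MAR processes, multiple imputation methods will be used". It names missing-not-at-random data as a possibility but attaches no method to it.
- **Primary outcomes.** The decrease in PSS-10 "score at 8 weeks will be our primary outcome", so the removal window closes at the primary time point.
- **Background.** The trial also studies the effect of the programme "as well as on the emergence of psychiatric disorders at 3- and 6-month follow-up". The secondary analyses cover PTSD, insomnia and depression at 3 and 6 months.
- **Procedure, week 4.** The mid-treatment assessment lists depression, PTSD and COVID-19 infection status. PSS-10 is not in that list.

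**The concern.** Intention to treat needs outcomes from everyone randomised, whatever happens to them afterwards. Here a rule ends participation because of an event after randomisation that goes with high stress, depression or PTSD scores. The scores lost are likely to be among the worst in their arm, and the loss is created by the protocol rather than by participants' own choice.

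Balance between arms cannot be taken for granted. The trial is open, and the CBT section describes an investigator call after a session has been missed for a week; no matching call is described for bibliotherapy. Unequal contact could make detection and referral differ by arm even if the treatments did not.

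At stake are the 8-week PSS-10 contrast and the 3- and 6-month symptom comparisons. A later analysis plan cannot recover questionnaires that were never sent.

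**Working it through.** **1. What the two sections imply together.** The Procedure section ends study participation at admission. The Statistical analyses section promises intention to treat but does not say whether those removed are still followed, or how they enter the analysis. If removal means what it ordinarily means, the 8-week, 3-month and 6-month scores do not exist and must be imputed.

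**2. What imputation has to work with.** Baseline scores exist. Depression and PTSD scores exist at week 4 for those admitted later. For an admission before week 4, only baseline questionnaires are common to both arms (the session-by-session visual analogue scales are completed in the CBT arm only). Missingness is then likely to depend on severity that was not observed, which is the case that missing-at-random imputation does not cover.

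**3. The plan's own figures.** The Sample size section states: "the expected values of PSS-10 at baseline are 23 ± 5 with a decrease to 19.6 ± 5 in the control group and 16 ± 5". The last of these values is for CBT. The difference, control minus CBT, is 19.6 − 16 = 3.6. With 46 per group, SD 5 and two-sided 5% (sidedness is not stated), power is 93.2%, which agrees with the claim of more than 90%. The total of 120 agrees with 92 × 1.30 = 119.6. Nothing in this point changes the sample size.

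**4. Illustrative size.** Inputs:
- Means among those retained: 16 (CBT) and 19.6 (control), from Sample size.
- n = 43 per arm: 120 × 0.9 × 0.8 / 2 = 43.2, applying the plan's 10% exclusions and 20% drop-outs in turn.
- PSS-10 of those admitted: 30. This is an assumption; the documents give no value.
- Admissions: k_T in CBT, k_C in control. Also assumed.

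Shift of the retained-only difference from the full difference, positive when it flatters CBT:

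shift = [k_T × (30 − 16) − k_C × (30 − 19.6)] / 43

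| k_T | k_C | Calculation | Shift (points) |
|---|---|---|---|
| 1 | 0 | 14 / 43 | +0.33 |
| 0 | 1 | −10.4 / 43 | −0.24 |
| 1 | 1 | (14 − 10.4) / 43 | +0.08 |
| 3 | 1 | (42 − 10.4) / 43 | +0.73 |
| 1 | 3 | (14 − 31.2) / 43 | −0.40 |

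The 1-to-1 row is not exactly zero because a common score of 30 is a larger excess over the CBT mean than over the control mean. With equal excess it is zero.

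For scale, the standard error of a simple comparison of two means with SD 5 is 5 × √(2/43) = 1.08, so a single CBT admission moves the estimate by about 0.3 of a standard error.

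**5. Range over the assumptions.** Let e be the excess score of those admitted over those retained, equal in both arms, and h_T and h_C the proportions admitted. Then shift = e × (h_T − h_C).
- Equal proportions: 0.
- 5% against 0%, e from 5 to 15: 0.25 to 0.75 points, with the sign set by the arm that has the admissions.
- 10% against 2%, e = 15: 15 × 0.08 = 1.2 points.

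Steps 4 and 5 model plain deletion. Imputation using baseline and week-4 scores would recover some of the shift, so for given inputs these figures lie towards the upper end.

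**The case against.** The case on the other side is that the documents support only an ambiguity. Much of that is right, and it rules out several stronger readings that a reader might infer.

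- **That the worst outcomes are deleted from the analysis.** The text does not say that data already collected are erased, or that the person leaves the intention-to-treat set. The sentence "No further data will be collected for these participants" follows the one on voluntary withdrawal and should not be read as the hospitalisation rule. An intention-to-treat set could keep these participants through baseline data and imputation.
- **That imputation would treat them as typical participants.** Imputation conditions on what was observed, so someone already deteriorating at week 4 could be imputed as worse than average. The plan also intends to examine which variables predict missingness.
- **That a harm is hidden.** The rule sits within the text on tracking undesirable outcomes, and a site must know of an admission to apply it. What is not stated is reporting by arm, which an article may leave to the full protocol.
- **That the trial excludes people for reaching its endpoint.** Psychiatric admission is not an endpoint. The primary outcome is PSS-10 and the others are short symptom scales. Admission is correlated with them, which is enough for the concern but is not the same thing.
- **That a fifth of the treatment effect is at risk.** The 3-to-1 case (0.73 / 3.6 = 20%) needs 3 of 43, or 7%, admitted to psychiatry within 8 weeks in one arm. Nothing in the documents supports that rate, and participants above the suicidal-ideation threshold are excluded at entry.

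The rule itself still stands against the objection. It says the study, it does not provide for continued questionnaires, and its natural reading creates the attrition that the analysis section sets out to minimise.

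**Conclusion.** The point holds as an inconsistency between the removal rule and the intention-to-treat promise, and it has a practical consequence: on the natural reading, the 8-week, 3-month and 6-month scores of some of the most severely affected participants would not be collected, and missing-at-random imputation may only partly make up for it.

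The direction of any bias is unknown and its size is probably small. With few admissions it is a few tenths of a point on a planned difference of 3.6, and about zero if admissions and excess scores are balanced. It passes one point only under strongly unequal admissions and a large excess score. All of these sizes rest on assumed admission counts and scores, since the documents give neither. The primary conclusion is not shown to be at risk. The change is worth making because it is cheap and because missed follow-up cannot be recovered later.

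**What to change.** Reconcile the Procedure and Statistical analyses sections by separating data collection from programme participation:

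1. State that a participant admitted to a psychiatric facility during the 8-week phase stays in the intention-to-treat set.
2. Continue to invite that participant to the 8-week, 3-month and 6-month questionnaires unless consent is withdrawn.
3. Record the admission and its date, and report admissions by arm.

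Whether the intervention continues after admission is a clinical matter, on which no view is given here.

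Cost: a change of wording in Procedure, one data field, and referral of the modification to the ethics committee, which the protocol requires for any change. Enrolment had not started at the stated protocol version, so no participant would be affected retrospectively if the change were made at that stage. The downside is that some questionnaires from these participants will be late or missing, so imputation will still be needed for part of the group.
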